## Abstract

**Background:**

Knee osteoarthritis (KOA) is a chronic musculoskeletal disease that can cause joint pain and dysfunction, affecting the quality of life of patients. Nonsurgical treatment is the conventional treatment of KOA, among which physical therapy is widely used because of its simplicity, convenience and effectiveness. The functional biomarker will add to the clinical fidelity and diagnostic accuracy. Therefore, our study chose a more objective evaluation indicator, functional near-infrared spectroscopy (fNIRS), to identify between healthy people and KOA patients, and to detect the pain change before and after treatment of KOA patients.

**Methods:**

The study will be conducted in the Rehabilitation Medical Center of West China Hospital of Sichuan University and divided into 2 stages. In the first stage, we will compare and determine the differences in baseline data between healthy volunteers and KOA patients. In the second stage, 72 KOA patients will be randomly divided into two groups: the drug therapy group (DT) and the combination therapy group (CT) for 10 treatments. Outcome measures will be measured at baseline and on the 5th and 10th days after the intervention, including the numerical rating scale (NRS), Western Ontario and McMaster Universities Osteoarthritis Index (WOMAC), pain catastrophizing scale (PCS), the association of pain severity with task-state functional connectivity fNIRS and association of pain severity with task-activated fNIRS.

**Discussion:**

By analyzing the fNIRS data of healthy volunteers and KOA patients, our study will be determined whether fNIRS can be used as a new indicator to reflect the severity of pain in KOA patients. Subsequently, the same fNIRS data for KOA patients before and after the intervention will be collected to provide an accurate evaluation criterion for the effect of physical therapy on KOA.

**Trial registration:**

The study was registered on the Chinese Registry website (registered in ChiCTR.org with the identifiers ChiCTR2200064175 and 29/09/2022).

## Background

Osteoarthritis (OA) is the most common degenerative joint disorder, causing chronic joint pain, physical function limitations and the reduction of quality of life (QoL) [1]. The main risk factors contributing to the initiation and progression of OA are aging, obesity and joint trauma [2, 3]. With the aging of the world, the prevalence of OA is gradually increasing, primarily focused on middle-aged and old people [2, 4]. Epidemiology investigations show that OA affects approximately 260 million people worldwide [5], accounting for 2.4% of the total number of disabled people in the world [2]. Knee osteoarthritis (KOA) is the most common type of OA. Musculoskeletal pain is the crucial symptom and primary reported outcome in KOA patients [6]. Furthermore, KOA pain is the major driver of functional limitations and the negative impact on quality of life [7]. Current KOA pain management therapies include nonpharmacological, pharmacological (NSAIDs), and surgical treatments [8]. Although drugs are effective for relieving pain, their analgesic capacity attenuates and causes adverse side effects over time [1].

To date, some clinical trials of treatments for KOA have demonstrated that physical therapy can effectively relieve pain and improve function, and also decreased the need for analgesic drugs [9, 10]. Recently, the combination of physical modalities has been widely discussed, such as low-intensity pulsed ultrasound (LIPUS) [11]. LIPUS is a physical therapy that is used to improve functional capacity in KOA [11, 12]. In addition, ultrashort wave therapy is also effective physiotherapy, which mainly depends on the thermal effect to relieve inflammation and pain in the knee joint [13].

In recent years, based on the development of neuroimaging techniques, studies on KOA disease-specific measurements have shown that many regions of the brain, such as the prefrontal cortex, the prefrontal lobe and the marginal area, are involved in the regulation of pain intensity [14]. Furthermore, Baliki et al. reported that the knee joint of KOA patients can activate the neural components of pain perception under pressure stimulation, and compared with the normal control group, the bilateral activity of the cerebral cortex and cingulate cortex of the patients increased significantly [15, 16]. Functional near-infrared spectroscopy (fNIRS) is a technology that quantifies cortical hemodynamics using noninvasive and portable means [17, 18]. The measurements in oxy- and deoxyhemoglobin concentrations represent the hemodynamic responses in the cerebral cortex [18]. FNIRS relies on the neurovascular mechanism of cerebral blood flow to record cerebral cortical activity. Respond to the activities of brain regions caused by spontaneous pain by recording the changes in hemoglobin concentration in the cerebral cortex [19]. The study summarized relevant brain regions in the fNIRS evaluation of pain state including Primary Motor Cortex (M1) (parietal, frontal, and temporal cortical regions) and Supplementary motor area (SMA) and so on [20]. Similarly, the results of the fNIRS evaluation of chronic pain (myofibrillary pain and back pain) showed motor cortex dysfunction in patients with pain [21]. A recent clinical study proved the feasibility of using fNIRS to evaluate the pain response in KOA patients and found that there was a certain correlation between the activation of the prefrontal cortex and pain in KOA patients [22]. Additionally, another study used fNIRS to explore the longitudinal effects of transcranial direct current stimulation (tDCS) on the hemodynamic response to pain in KOA patients and found that cortical activity increased over time [23]. Research on physical factor therapy based on fNIRS to improve the pain of KOA patients is still relatively limited. Therefore, our study introduces a new detection method to evaluate physical therapy for relieving pain and dysfunction in KOA patients and provides a new choice for the clinical evaluation of OA severity.

## Methods

The trial will be divided into two stages. The first stage is to analyze the baseline data of healthy volunteers and KOA patients and compare the differences between the two groups. In the second stage, the KOA patients will be randomly divided into two groups, and the outcome indicators will be analyzed after the intervention. This stage is a single-center, single-blinded, parallel randomized controlled trial (RCT). The trial will follow the Recommendations for Interventional Trials [24], and the flow diagram is shown in Fig. 1. The trial will be conducted in West China Hospital, Sichuan University, Chengdu, China. All participants will sign written informed consent forms.

**Fig. 1 Fig1:**
[figure not shown]
Flow chart of the second stage

### Participants

Two trained rehabilitation physicians will recruit 24 healthy volunteers over 50 years old and 72 KOA patients according to the inclusion and exclusion criteria. Patients should meet the following conditions: (1) diagnosed with KOA according to the 2021 Chinese Orthopedics Association diagnosis and treatment guidelines [25]; (2) knee pain (previous week) score ≥ 3 on the NRS; (3) Kellgren–Lawrence grade I-III [26]; (4) right-handed; (5) normal lower limbs; and (6) no open wounds or metal foreign bodies near the knee joint.

The exclusion criteria were as follows: (1) diagnosed with rheumatoid arthritis, gout or severe osteoporosis; (2) having undergone knee surgery or received an intra knee injection within the past 6 months; (3) experiencing depression (using the Self-rating depression scale, depression severity index < 0. 50 is no depression [27]), anxiety (using the Self-rating Anxiety Scale, standard score < 50 is no anxiety [28]), mania (using the Bech-Rafaelsen Mania Scale, ≤ 5 is no mania [29]), dementia and obvious cognitive impairment (using the Montreal Cognitive Assessment, ≥ 26 is normal [30]); (4) having a cancerous tumor, severe bronchiectasis, acute suppurative inflammation, high fever, active pulmonary tuberculosis, glaucoma, heart failure, severe anemia, cerebrovascular disease, or having a pacemaker implanted in the body; (5) having a history of epilepsy or taking antiepileptic drugs; (6) taking drugs that change the excitability of the cerebral cortex (such as sedative-hypnotics or antidepressants); (6) unable to participate in the trial due to other health problems; and (7) unable to sign the informed consent or participate in other scientific research projects(for example, a sudden fall, sudden low back pain, shoulder pain and other sudden diseases).

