### Sample size

The sample size will be determined by comparing the NRS scores before and after treatment based on a preliminary study of the first 10 participants. With a yielding power of 90% and a significance level of 0.05, using G*Power (3.1.9.4) software, the sample size is intended to consist of 30 participants in each group. With a 20% dropout rate, the two groups required 72 participants. KOA patients and healthy volunteers will be calculated in a ratio of 3:1, for a total of 24 healthy volunteers.

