## Statistical analysis

Data analysis will use an intention-to-treat analysis strategy. Data analyses will use SPSS (26.0). P ≤ 0.05 will be significantly different. The raw data collected by fNIRS will be preprocessed by NIRSPARK software, including artifact processing, filtering, segmentation and baseline comparison. At the same time, the fNIRS data will be analyzed using the statistical analysis module of MATLAB (R2020a). Component comparability of baseline data between the two groups will be performed using the chi-square test and independent samples t test. The frequency and percentage of count data will be calculated in the statistical description; the data of measurement data following a normal distribution will be described by the mean ± standard deviation. For the comparison between groups after the intervention, the independent samples t test will be used if the data follow a normal distribution, and the Mann‒Whitney U rank sum test will be used if the data are nonnormally distributed. For intragroup comparisons before and after the intervention, a paired t test will be used if the data follow a normal distribution, and the Wilcoxon rank sum test will be used for data that are not normally distributed.

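### The non-randomised Stage 1 contrast of healthy volunteers with KOA patients has no common age limit, matching or adjustment, so an fNIRS difference cannot be attributed to knee pain

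*Protocol article*

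**What the plan says.** The Abstract (Methods) sets the aim of Stage 1: to "compare and determine the differences in baseline data between healthy volunteers and KOA patients". The Methods section repeats it: "The first stage is to analyze the baseline data of healthy volunteers and KOA patients and compare the differences between the two groups".

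Under Participants, the physicians will "recruit 24 healthy volunteers over 50 years old and 72 KOA patients", applying the listed inclusion and exclusion criteria. The six inclusion items that follow are worded for patients. They cover the diagnosis, absence of wounds or metal near the knee, and "2) knee pain (previous week) score ≥ 3 on the NRS; (3) Kellgren–Lawrence grade I-III [26]; (4) right-handed; (5) normal lower limbs". None of them is an age limit, and neither is any exclusion item.

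Under Sample size, the number of volunteers follows from a ratio alone: "KOA patients and healthy volunteers will be calculated in a ratio of 3:1, for a total of 24 healthy volunteers". No matching variable is named. The power statement in the same section ("With a yielding power of 90% and a significance level of 0.05, using G*Power (3.1.9.4) software") belongs to the comparison of NRS pain scores before and after treatment, not to Stage 1.

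Under Statistical analysis, the baseline comparison reads: "Component comparability of baseline data between the two groups will be performed using the chi-square test and independent samples t test". The other tests named there are Mann-Whitney, paired t and Wilcoxon tests. The fNIRS data go to a MATLAB statistics module that is not described further. No covariate is mentioned.

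fNIRS is recorded during chair stands, an up-and-go test, a fast 40-m walk, stair climbing (Primary outcomes) and a 6-minute walk (Secondary outcomes). No speed or cadence is imposed on any of them.

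**The concern.** Stage 1 supports a large claim. The Abstract opens by offering fNIRS as a way to tell healthy people from KOA patients, and its Discussion uses the data of both groups to judge whether fNIRS reflects pain severity. The closing section presents fNIRS as a new objective diagnostic index for KOA. It lists the added healthy group as the first advantage of the study, while its limitations cover only follow-up and blinding.

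Randomisation does not protect this contrast. The Background ties age and body weight to having the disease, so the groups can be expected to differ on them unless the design prevents it. If the fNIRS signal also varies with age, sex, BMI or the amount of movement, a difference between groups can arise with no contribution from pain. Confounding could equally hide a real difference.

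**Working it through.** **1. The plan's own figure.** 72 patients / 3 = 24 volunteers. This reproduces exactly and confirms that the number comes from a ratio, not from a matching scheme or a Stage 1 power calculation.

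**2. The two groups side by side.**

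| Feature | Volunteers | Patients |
|---|---|---|
| Number | 24 | 72 |
| Age limit | over 50 | none stated |
| Handedness | not stated | right-handed |
| Matching on age, sex, BMI | none named | none named |

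**3. How large a spurious difference could be.** The article gives no age, sex or BMI distribution and no correlation with the fNIRS signal, so these are assumptions:

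- g = gap between the groups on a confounder, in within-group SDs, from 0.25 to 1.0;
- r = within-group correlation of the confounder with the signal, from 0.2 to 0.5;
- no pain effect;
- a two-sided 5% t test (the article gives P ≤ 0.05 without sidedness).

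The spurious standardised difference is d = g × r. For 24 versus 72, the non-centrality parameter is d / √(1/24 + 1/72) = d × √18 = 4.243 × d, on 24 + 72 − 2 = 94 degrees of freedom. At g = 1.0 and r = 0.5, for example, d = 0.50 and the non-centrality is 2.12.

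Chance that the unadjusted test is significant (d in brackets):

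| g | r = 0.2 | r = 0.3 | r = 0.5 |
|---|---|---|---|
| 0.25 | 5.5% (0.050) | 6.1% (0.075) | 8.2% (0.125) |
| 0.50 | 7.0% (0.100) | 9.7% (0.150) | 18.3% (0.250) |
| 0.75 | 9.7% (0.150) | 15.7% (0.225) | 35.0% (0.375) |
| 1.00 | 13.4% (0.200) | 24.3% (0.300) | 55.6% (0.500) |

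The low end is almost the nominal 5%; the high end is about eleven times nominal (55.6 / 5 = 11.1). Each cell is for one confounder. Several could add up or cancel.

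**4. Why later adjustment is only a partial remedy.** If patients aged 50 or younger are enrolled, no volunteer of that age exists to compare with them, and a regression on age must extrapolate. Overlap has to be secured at recruitment.

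**The case against.** **Covariates belong in an analysis plan that is not shown, and the MATLAB step is undefined.** This is fair as far as covariates go: adjustment in an unseen document cannot be excluded. It does not cover who is recruited, which the article sets out itself.

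**The two groups in the baseline sentence may be the randomised arms.** The wording allows that, since the same paragraph goes on to comparisons after the intervention. In that case the article names no Stage 1 test beyond the undefined module, and adjustment is still not mentioned.

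**The ages may be similar in practice.** The Background places the disease mainly in middle-aged and older people, and the cited diagnostic guideline, which is not shown, might carry an age element. Both points argue for the lower part of the range. Neither equalises age, sex or BMI among people over 50.

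**Slower movement may be a result of knee pain.** This stands. Movement would then be partly a mediator, and adjusting for it could remove part of the effect of interest. That slower movement will occur is itself an expectation, not something the article reports.

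**The pain claim does not rest on Stage 1 alone.** The fNIRS outcomes are associations with pain severity, and comparisons between patients with different levels of pain do not depend on the volunteers. This is true, but the Abstract still draws on the healthy-versus-KOA data for the pain claim.

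Stronger readings that a reader might infer, and that the article does not support:

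- *Volunteers face no criterion except age.* Both groups are recruited under the inclusion and exclusion criteria, and the exclusion list (psychiatric, cognitive, epilepsy and drug items among others) is not restricted to patients. It plausibly covers volunteers. The handedness item is worded for patients only.
- *A non-significant baseline test will be taken as proof that volunteers and patients are comparable.* No text says this; Stage 1 looks for differences.
- *The Stage 2 treatment comparison is confounded too.* Those arms are randomised. Task performance at days 5 and 10 is measured after randomisation and may respond to treatment, so using it as a covariate there could bias the treatment effect.

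**Conclusion.** The point holds for Stage 1 only. As described, a healthy-versus-KOA difference in fNIRS cannot be separated from differences in age, sex or BMI, nor from the amount and speed of movement during the tasks. It should not be reported as an effect of pain.

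The range of about 5.5% to 56% false-positive findings illustrates what the assumed gaps and correlations would do; it is not an estimate for this trial. Nothing in the article supports a gap as large as 1 SD, so the top of the range should not be read as expected. The flaw in the design does not depend on where in the range the truth lies.

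**What to change.** Before volunteer recruitment is complete:

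1. Align the age criterion across the two groups.
2. Frequency-match the 24 volunteers to the age bands and sex split of the enrolled patients.
3. State that the handedness criterion and the exclusion list apply to volunteers.

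In the analysis:

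4. Analyse each Stage 1 fNIRS measure with a linear model on group, age, sex and BMI, and report the adjusted group difference with its confidence interval.
5. Record task performance (stands completed, seconds, speed), which the tests already generate. Add one sensitivity estimate that includes it, and say in the report that it may sit on the path from pain to signal.
6. Leave task performance out of the Stage 2 models.

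The cost is slightly slower volunteer recruitment, a few recorded fields and some analysis wording. The main model uses three more degrees of freedom than the t test (96 − 5 = 91 instead of 94), and the sensitivity model one more for each performance term.

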### Interventions

In the first stage, 24 healthy volunteers and 72 KOA patients will not receive any treatment, with only one baseline data measurement. In the second stage, 72 patients with KOA will be randomly divided into two groups: the drug therapy group (DT) and the combination therapy group (CT).

#### Drug therapy group (DT)

*Education*: The patients will receive a doctor's oral education after grouping, including disease introduction, common rehabilitation treatment methods, weight management, emotional management, and daily exercise-related precautions.

*Drug*: All patients should take glucosamine hydrochloride capsules and celecoxib capsules orally [25].

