#### Combination therapy group (CT)

The combination therapy group included the same education and drug as the DT, along with 10 sessions of physical therapy.

*Physical therapy*: patients will receive 2 courses of physical therapy, including 10 sessions of ultrashort wave therapy (Shantou Medical Equipment Factory Co., Ltd., China) and LIPUS (Shenzhen Dongdixin Technology Co., Ltd., China). Ultrashort wave therapy takes 20 min for each knee joint, and the treatment intensity is based on the patient's feelings, that is, there is a feeling of warmth during treatment. LIPUS takes 5 min for each knee joint, and the treatment intensity is 1.4 W/cm^2^. All treatments will be performed by two trained physiotherapists to ensure therapeutic efficacy.

During the trial, patients’ condition is aggravated, and they can be allowed to use relevant drugs for treatment. However, any medication use will be recorded in the medical record and diary.

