### Blinding

This trial is single-blinded. Patients could not be blinded due to the treatment method, but each patient would only know their trial protocol at randomization. Before the start of the trial, standardized training will be given to the researchers. After grouping, an independent person will inform the researchers of the grouping, and the researchers only know the patients in this group. Evaluators, statisticians and data managers will be blinded during the trial.

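### The education shared by both arms is given after allocation, which leaves an avoidable risk that it is delivered or received differently by arm

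*Protocol article*

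**What the plan says.** Under Drug therapy group (DT), the article sets the order and content of a talk by a doctor: "oral education after grouping, including disease introduction, common rehabilitation treatment methods, weight management, emotional management". Precautions for daily exercise complete the list of topics. Under Combination therapy group (CT), it commits to the same component in the other arm: "The combination therapy group included the same education and drug as the DT, along with 10 sessions of physical therapy".

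Under Randomization, allocation follows the baseline measurement and uses opaque envelopes handled by someone independent of the study. Under Blinding, patients cannot be blinded and learn their treatment at randomisation. On staff, that section makes three statements:

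- Researchers are trained to a common standard before the trial begins.
- Once patients are allocated, the arm is disclosed to researchers: "After grouping, an independent person will inform the researchers of the grouping, and the researchers only know the patients in this group".
- Three roles are to stay blinded: those who assess outcomes, those who analyse the data and those who manage it.

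Under Primary outcomes, the first primary outcome is knee pain on the 0 to 10 NRS. Under Secondary outcomes, WOMAC and PCS are described as self-assessed. Under Statistical analysis, the groups are compared after the intervention by an independent samples t test or a Mann-Whitney U test.

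**The concern.** The comparison of CT with DT isolates physical therapy only if everything else is the same in both arms. The drugs are a defined product. The education is a conversation, so its content, tone and emphasis can shift with what the speaker and the listener know. The article places that conversation at a point where the listener certainly knows the arm and the speaker may know it.

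Two of the listed topics make this more than a formality. Common rehabilitation methods are the class of treatment that CT is about to receive and DT is not, so the same words describe a coming treatment to one patient and a withheld one to the other. Emotional management bears on how patients think about pain, which is what PCS measures.

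At stake is performance bias in the patient-rated outcomes: part of an observed difference in NRS, WOMAC or PCS could come from the talk and not from ultrashort wave therapy and LIPUS. Blinded evaluators do not prevent this, because the patient supplies the score.

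**Working it through.** The document gives no figure on this point, so there is none to reproduce. The check sets its statements side by side.

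1. **Order.** Randomization puts allocation after baseline, and the education paragraph puts the talk after grouping. The sequence is therefore baseline, allocation, talk, treatment. This is a stated rule, not a detail left to a fuller document.
2. **Who knows the arm at the talk.** The patient does (Blinding). For the doctor the article is silent: the list of blinded roles covers evaluators, statisticians and data managers, and the educating doctor is not on it. Absence from that list does not show that the doctor is told the arm.
3. **Who gives the talk.** The education paragraph speaks only of a doctor. The Blinding section speaks of researchers: "an independent person will inform the researchers of the grouping, and the researchers only know the patients in this group". The natural reading is that researchers are separated by arm, but the wording is unclear, and nothing says that the educating doctor is one of them.
4. **What protects equality.** CT is promised "The combination therapy group included the same education and drug as the DT", and researchers are trained before the start. The first states an intention. The second does not describe its content and covers the educator only if the educator counts as a researcher. Neither changes what the patient knows when listening.
5. **Which outcomes are exposed.** NRS, WOMAC and PCS, all rated by the patient.

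**Why no size can be given.** The effect on the test depends on two unknowns: whether educators are split by arm, and how much of the outcome variance depends on the educator (an intraclass correlation, ρ). Neither is in the document. The illustration below assumes one educator per arm, total variance 1 and m = 30 analysed per arm (the figure under Sample size).

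- Variance of the mean difference as the test sees it: about 2(1 − ρ)/m.
- True variance: 2[ρ + (1 − ρ)/m].
- Ratio of standard errors: r = √{[ρ + (1 − ρ)/m] / [(1 − ρ)/m]}.
- True two-sided type I error at nominal 5%: 2[1 − Φ(1.96/r)].

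For ρ = 0.05: (1 − 0.05)/30 = 0.0317; r = √(0.0817/0.0317) = 1.606; 1.96/1.606 = 1.22; type I error about 22%.

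| Assumed ρ | r | True type I error |
|---|---|---|
| 0 | 1.000 | 5.0% |
| 0.01 | 1.142 | 8.6% |
| 0.02 | 1.270 | 12.3% |
| 0.05 | 1.606 | 22.2% |
| 0.10 | 2.082 | 34.6% |

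If the same doctors serve both arms with the same content, the educator adds no such inflation and the error stays at 5% whatever ρ is. The table therefore runs from no effect to a large one on assumptions alone. It shows why shared educators matter and does not estimate a bias in this trial.

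**The case against.** The strongest case against is that the article promises the same education in both arms and trains its researchers, and that background care after allocation is ordinary practice. Who gives the talk, and whether it is scripted, are details that a journal article commonly leaves to the full protocol. This stands in part: the absence of a named educator or a script is not itself a fault. What remains is the order, which the article states outright.

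A reader might infer more: that the doctor knows the arm, that each arm has its own educator, and hence that educator and treatment are fully confounded and no analysis could separate them. The document does not support this as fact. It does not identify the educating doctor with the researchers who are told the grouping, and its sentence on those researchers is ambiguous. Confounding is a conditional risk here.

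It can also be said that expectation in CT and disappointment in DT come from knowing the arm, wherever the talk is placed. That is right, and moving the talk does not remove them. It does stop the allocation from shaping how the talk is given and heard.

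Finally, describing rehabilitation methods before allocation might strengthen a preference for CT. This carries little weight, because a consenting patient would be expected to know already that physical therapy is what is being randomised.

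**Conclusion.** The point holds as an avoidable weakness in a stated rule. The shared education is placed after allocation, when patients know their arm and the educating doctor is not listed as blinded, and three patient-rated outcomes, one of them primary, are exposed. The promise of the same education and the general training of researchers do not close this route.

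The size cannot be derived from the document, and no particular shift in NRS, WOMAC or PCS is claimed. Confounding of educator with arm would follow only if educators were split by arm as the researchers appear to be, which the article does not say. The finding does not show that the trial's comparison is invalid. It calls for a cheap improvement, worth making because the remedy costs almost nothing.

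**What to change.** In the education paragraph, change the order so that the talk follows the baseline measurement and precedes the opening of the envelope, with the same doctor or doctors giving the same talk to every patient. At that point neither doctor nor patient can know the allocation. Because the talk still comes after baseline, the first-stage comparison of patients with healthy volunteers is untouched.

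In the Blinding section, state that staff who deliver components common to both arms are not divided by arm.

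The cost is one change of order and one sentence, with no extra visits or staff. There are two limits: a patient who declines randomisation after the talk will already have received it, and expectation effects from knowing the arm during treatment remain.
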